## Abstract

**Background:**

There are gaps between what family practitioners do in clinical practice and the evidence-based ideal. The most commonly used strategy to narrow these gaps is the printed educational message (PEM); however, the attributes of successful printed educational messages and their overall effectiveness in changing physician practice are not clear. The current endeavor aims to determine whether such messages change prescribing quality in primary care practice, and whether these effects differ with the format of the message.

**Methods/design:**

The design is a large, simple, factorial, unblinded cluster-randomized controlled trial. PEMs will be distributed with ***informed***, a quarterly evidence-based synopsis of current clinical information produced by the Institute for Clinical Evaluative Sciences, Toronto, Canada, and will be sent to all eligible general and family practitioners in Ontario. There will be three replicates of the trial, with three different educational messages, each aimed at narrowing a specific evidence-practice gap as follows: 1) angiotensin-converting enzyme inhibitors, hypertension treatment, and cholesterol lowering agents for diabetes; 2) retinal screening for diabetes; and 3) diuretics for hypertension.

For each of the three replicates there will be three intervention groups. The first group will receive ***informed ***with an attached postcard-sized, short, directive "outsert." The second intervention group will receive ***informed ***with a two-page explanatory "insert" on the same topic. The third intervention group will receive ***informed***, with both the above-mentioned outsert and insert. The control group will receive ***informed ***only, without either an outsert or insert.

Routinely collected physician billing, prescription, and hospital data found in Ontario's administrative databases will be used to monitor pre-defined prescribing changes relevant and specific to each replicate, following delivery of the educational messages. Multi-level modeling will be used to study patterns in physician-prescribing quality over four quarters, before and after each of the three interventions. Subgroup analyses will be performed to assess the association between the characteristics of the physician's place of practice and target behaviours.

A further analysis of the immediate and delayed impacts of the PEMs will be performed using time-series analysis and interventional, auto-regressive, integrated moving average modeling.

**Trial registration number:**

Current controlled trial ISRCTN72772651.

## Background

There are gaps between the evidence-based, ideal clinical practice and what family practitioners (FPs) actually do. We understand very little about the reasons for these gaps [1]. Printed educational messages (PEMs), ranging from short directive statements to long guidelines, have often been used in the hope of narrowing these gaps [2], but there is profound uncertainty around their usefulness [3-5]. PEMs fell into disfavour among researchers in this field after a 1997 systematic review found their effects to be uncertain [6]. A recent larger overview found a median absolute improvement of 8% (range 4–17%) [7].

However, no review can overcome the limitations of the primary evidence: the small number of trials (each one of which is small in size), and their continued methodological weaknesses (insufficient power to detect modest effects, and unit of analysis errors).

## Aims and objectives

1. To conduct a large, reliable and relevant (pragmatic), randomized controlled trial of the effect of printed educational messages (PEMs) on guideline adherence among Ontario primary care physicians.

2. To determine whether there is any difference in impact on physician guideline adherence between: 1) a postcard-sized, short, directive message, 2) a two-page, longer, explanatory message, or 3) a combination of both.

3. To determine the relative effectiveness of PEMs in narrowing gaps for different health problems.

A randomised trial will help define the role of PEMs, while increasing our understanding of the process of implementing evidence of effectiveness into daily clinical care [8,9].(In Canadian research, the word 'translation' is used, in place of 'implementation'.)

## Methods/design

Pragmatic, randomized controlled trials are reliable evaluations of the effectiveness of often complex health care interventions carried out under real-world conditions [8,9].

Effectiveness of the intervention usually is assessed by impact on simple outcomes of importance to users of the intervention, such as: death, disability, user satisfaction, utilization of care, and quality of life. Pragmatic trials are attuned to the same criteria of effectiveness as those used by policymakers – important and visible outcomes in usual health service planning entities, and under typical service limitations. Pragmatic trials take into account the varied ways that interventions are implemented in the real world. In contrast, classic explanatory randomized trials (efficacy trials) test the effects of an intervention, often a drug, under idealised and tightly controlled conditions, and on narrowly defined groups of individual patients. Classic efficacy trials usually are carried out to advance medical knowledge, whereas pragmatic trials are concerned with assessing the effects of interventions as they are usually used, in typical settings, and on typical users.

### Choice of target physician practices

We used several criteria to identify evidence/practice gaps important in primary care: the gap involves a common disorder in Canadian primary care; evidence-based practice is not constrained by structural, financial or other barriers; the evidence/practice gap is large and may cause patient harm or unnecessary cost; well-tested process indicators exist that are measurable using administrative datasets; and the gaps span a range of clinical practice behaviours.

As a result, we selected three evidence-practice gaps leading to clinical choices that family doctors should make more often. These gaps are based upon Ontario administrative data.

1. Prescription of angiotensin-converting enzyme (ACE) inhibitors, aggressive hypertension treatment, and cholesterol-lowering treatment for persons with diabetes (each falls short of guideline targets by at least 30%) [10-33].

2. Referral of persons with diabetes for eye screening by an optometrist or ophthalmologist (50% below guideline-recommended levels) [34-40].

3. Prescription of diuretics as first-line therapy for newly diagnosed hypertension (~40% below guideline-recommended levels) [41-50].

### Trail intervention: the printed educational messages

We will develop PEMs to address each of the three identified evidence/practice gaps, using input from a diverse group of physicians to identify barriers to evidence-based practice and from a communications consultant to inform design of the messages [51].

The PEMs will be distributed along with ***informed***, a peer-reviewed, evidence-based practice synopsis, which has been mailed quarterly since 1994 to nearly 15,000 primary care providers in Ontario. Subscription is voluntary and is at no cost to the subscriber. Articles for each eight-page issue are developed by clinical and research staff from the Institute for Clinical Evaluative Sciences (ICES), Toronto, Canada.

Two PEMs will be developed for each of the three evidence/practice gaps:

• A short, directive, evidence-based PEM on a postcard-sized card (referred to as an outsert) stapled to the lower-left quarter of the front page of ***informed***.

• A longer two-page insert (indistinguishable from the rest of the periodical in size, style and editing) focusing on the same topic as the outsert, but excluding the directive statements and including more background, evidence-based guidelines and references.

### Research design

The research design is a factorial, cluster-randomized controlled trial with three replicates [52,53]. ***informed ***is published four times per year. We will conduct three replicates of the trial to cover the three evidence-practice gaps over a nine-month period (three successive mailouts of ***informed***). We will test the effects of short (directive) and long (discursive) PEMs compared with no PEM on the clinical practices of primary care physicians, and on related patient outcomes. Table 1 describes the intervention groups for each of the three replicates. In the first replicate (ACE inhibitors, hypertension treatment, and cholesterol-lowering agents for diabetes), the first intervention group will receive a copy of ***informed ***with both the short, directive, evidence-based outsert stapled to the lower-left quarter of the front page, and the longer two-page insert focusing on the same topic as the outsert. The second intervention group will receive the identical ***informed***, with only the above-mentioned outsert. The third intervention group will receive the identical copy of ***informed ***with the above-mentioned insert. The control group will receive the identical ***informed ***only, without the insert or the outsert. The health care topic shared by the insert and outsert will not be covered elsewhere in that issue of ***informed***. The outsert for this first replicate is shown in Figure 1 and the insert in Figures 2 and 3.

**Figure 1 F1:**
[figure not shown]
Printed educational message "outsert" for replicate 1.

**Figure 2 F2:**
[figure not shown]
Printed Educational Message "Insert" for Replicate 1 (part 1).

**Figure 3 F3:**
[figure not shown]
Printed Educational Message "Insert" for Replicate 1 (part 2).

**Table 1 T1:** Description of the intervention groups within each of the three replicates

***REPLICATE 1: Assertive hypertension and cholesterol treatment in patients with Diabetes***			
		**INSERT**	**No INSERT**
**OUTSERT**		1. Insert & Outsert	2. Outsert only
**NO OUTSERT**		3. Insert Only	4. No PEM
			
***REPLICATE 2: Retinal Screening for Patients with Diabetes***			
		**Insert**	**No insert**

**OUTSERT**	*Patient Reminder Note*	1. Insert & Outsert & Patient Reminder	2. Outsert & Patient Reminder Note
	*No Patient Reminder Note*	3. Insert & Outsert	4. Outsert only
**NO OUTSERT**		5. Insert Only	6. No PEM
			
***REPLICATE 3: Diuretics for first-line treatment of hypertension***			
		**Insert**	**No insert**

**OUTSERT**	*Theory-based Outsert*	1. Insert & Theory-based Outsert	2. Theory-based Outsert Only
	*Non-theory-based outsert*	3. Insert & Non-theory-based Outsert	4. Non-theory-based Outsert only
**NO OUTSERT**		5. Insert Only	6. No PEM

For the second replicate (retinal screening in patients with diabetes), in addition to the short, directive outsert and the longer, explanatory insert, we will add a reminder note that physicians could give to their patients to supplement the verbal reminder that we encourage physicians to give. Because it is not clear whether this patient-held reminder to make an appointment with their eye care provider is any more effective than the verbal reminder that we will encourage physicians to give, we will randomize those physicians receiving an outsert to receive a pad of the patient-aimed reminder slips.

For the third replicate (using thiazides as first-line treatment for hypertension), we will use *two *different short-directive outsert messages (in addition to the long, explanatory insert message). Our OPEM team will develop the first outsert message, whereas a team of psychologists with experience in knowledge implementation and the use of psychological theories will develop the second outsert message. With the addition of a theory-based outsert, we will be able to determine whether a message that is based on psychological theory, specifically on the *Theory of Planned Behaviour*, will be more effective in changing clinical behaviour toward more evidence-based practice than a message that is based on 'standard' methods, which are uninformed by an explicit theoretical basis[54]. (See "Ancillary Studies" below.)

### Allocating participants to trial groups

Trials of interventions aimed at changing clinical practices must be randomized at the level at which they are directed – that is, at the level of the doctor, not his or her patients. In group practices, however, doctors may well share information. To prevent contamination, randomization must take place at the level of the group rather than the individual practitioner. A group practice is defined here as all primary care physicians who share a common street address, or who share a common office number in a multi-office building. The eligible Ontario primary care doctors will be fee-for-service family physicians (FPs) and general practitioners (GPs) (Ontario Health Insurance Program [OHIP] billing code 00).

These practitioners will be identified from the health care providers database held at ICES. They will be verified to be in active practice. In order to enable prescribing outcomes to be measured, we will ensure that they have an adequate volume of seniors among their patients by requiring that they write at least 100 prescriptions appearing in the ODB (Ontario Drug Benefit Program) database in the year prior to enrollment. The physician identifier obtained from these ODB claims first will be linked to the physician's College of Physicians and Surgeons of Ontario (CPSO) number at ICES. Addresses of practitioners will be obtained by hand-linking the CPSO number to the CPSO database, which is publicly available on the Internet. The CPSO website can be queried by CPSO number and will supply physician name and practice address.

All FPs and some GPs are already on the ***informed ***mailing list. Those who are not currently on the list will be added for the three intervention issues of ***informed***. This list will be sorted by addresses of practitioners into practices, in order to prevent practitioners with the same address, who may share administrative staff or communicate readily with each other, from being randomized to different groups (i.e., to reduce contamination). Using a computer-generated sequence of random numbers, the practices will then be randomized to one of the intervention groups. For each of the three replicates, we will re-randomize physician practices to one of the intervention groups.

The relevant patients for each practice are defined as any patient attending that practice who meets study entry criteria. For each of the gaps, we are using a different algorithm to identify relevant patients (see Table 2). A patient may be counted multiple times, as they are free to attend more than one primary care practice. This approach is conservative, and gives all physicians "credit" for appropriate prescribing or referral decisions made by any of the physicians who saw that patient during the study period. In a sensitivity analysis, we will use a more rigorous rule for defining physician-patient relationships, whereby patients will be assigned only to the primary care provider with whom they had a plurality of their visits. In a tie, the patient will be assigned to the primary care physician who wrote the greatest number of their prescriptions during the study period. Patients who still cannot be unambiguously assigned will be allocated randomly to one of the practitioners who have written prescriptions for them during the study period.

**Table 2 T2:** Patient population and primary outcome for each of 3 replicates

**Replicate**	**Evidence/Practice Gap**	**Patients studied**	**Expected patient N**	**Primary Outcome**
1	Use of ACE inhibitors, blood pressure and cholesterol-reducing drugs (ABCs); each fall short of guideline targets by at least 30%	All prevalent cases of persons with diabetes, aged ≥ 65 years	280,000	% of target patients receiving an ACE inhibitor, % receiving 2 or more antihypertensive, and % receiving lipid-lowering drug
2	Retinopathy screening in incident Type 2 DM; 50% below guideline-recommended levels	All incident cases of persons with diabetes, aged >30 years	100,000	% of target patients receiving complete eye exam from optometrist or ophthalmologist
3	Use of hydrochlorothiazide (HCTZ) as initial therapy in uncomplicated hypertension; ~40% below guideline-recommended levels	All patients ≥ 65 years, newly initiated on antihypertensive therapy	30,000	% of target patients receiving a diuretic

The Registered Persons Database (RPDB) identifies all persons in the province who are eligible for OHIP coverage. It will be used to link patient participants to the administrative databases, and to detect death and out-migration of patients over the course of the study. Claims from the ODB Program will be used to measure the prescribing changes that result from the interventions. These data are available only for people 65 years of age and older. Accordingly, the two drug-related replicates are restricted to that age group of the Ontario population. The ODB data are delivered to ICES within two weeks of the end of the month of the claim. Claims data from OHIP will be used to identify physician patient linkages, and to measure the delivery of ophthalmologic and optometric screening. All of these datasets are available at ICES, and all bear encrypted health card numbers that are unique to patients but common over time and across data sets.

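### The single-assignment sensitivity analysis counts visits doctor by doctor although practices are randomised, so a patient of several practices can be placed in one they attended less

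*Protocol article*

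**What the plan says.** All of the following is in the Protocol article, mostly under Allocating participants to trial groups.

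- **Randomised unit.** Because doctors in a group may share information, "randomization must take place at the level of the group rather than the individual practitioner". Membership of a group is settled by address (or by office number in a multi-office building), and on that basis "the practices will then be randomized to one of the intervention groups".
- **Main attribution rule, by practice.** "The relevant patients for each practice are defined as any patient attending that practice who meets study entry criteria". Double counting is accepted: "A patient may be counted multiple times, as they are free to attend more than one primary care practice".
- **Sensitivity rule, by doctor.** Under the stricter rule, "patients will be assigned only to the primary care provider with whom they had a plurality of their visits". Ties are settled by comparing how many prescriptions each individual physician wrote for the patient over the study. Anyone still unassigned goes at random to one of the practitioners who prescribed for them. The two tie-break steps show that the provider in the first step is an individual doctor.
- **Model.** The Analyses section accounts for clustering of patients within practices.
- **Data.** The same section as the rule says that prescribing is measured from Ontario Drug Benefit (ODB) claims, available only from age 65. Table 2 defines replicate 2 as incident diabetes above age 30.

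**The concern.** All doctors at one address are in the same arm, so for assigning an arm the relevant question is which practice the patient used most. Taking the plurality doctor by doctor answers a different question. A practice whose visits are spread over several doctors can lose the patient to a practice with fewer visits in total, because no single one of its doctors has the most.

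This analysis is the plan's check on counting a patient in several practices at once. If some patients are scored in a practice they used less, usually one in another arm, the check is blurred. Avoidable ties also send patients to a prescription rule that, for part of replicate 2, has no data behind it.

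**Working it through.** **1. The plan's own figures.** No stated figure depends on this rule. For completeness, the power claims under Proposed sample size are consistent with a normal-approximation check (baseline 36%, intra-class correlation 0.092, 1250 practices per arm, two-sided alpha 0.05):
- 10 patients per practice: design effect 1 + 9 × 0.092 = 1.828; effective n = 12,500 / 1.828 = 6838 per arm; power for 36% against 41% is above 99.9% (stated: more than 97%).
- 3 patients per practice: design effect 1 + 2 × 0.092 = 1.184; effective n = 3750 / 1.184 = 3167; power 98.3%.

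**2. The rule applied to single patients.**

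| Visits in A | Visits in B | Highest single doctor, A : B | Rule gives | Practice totals, A : B |
|---|---|---|---|---|
| 3 + 3 | 4 (one doctor) | 3 : 4 | B | 6 : 4 |
| 2 + 1 | 2 (one doctor) | 2 : 2 | tie | 3 : 2 |
| 2 + 2 (two-doctor practice) | 3, all to one doctor of a five-doctor practice | 2 : 3 | B | 4 : 3 |

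Two conditions are needed: the patient attends at least two practices, and sees at least two doctors in the leading one. A patient who stays within one practice is unaffected, since all its doctors share an arm.

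**3. Chance that the chosen practice is in another arm.** With independent allocation this is 1 − Σ(allocation share)².
- Replicate 1, four arms of 1250: 1 − 4 × 0.25² = 75%.
- Replicates 2 and 3, two arms of 1250 and four of 625 (total 5000, shares 0.25 and 0.125): 1 − (2 × 0.25² + 4 × 0.125²) = 1 − 0.1875 = 81.25%.

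**4. How often.** The article gives no visit distribution, so this rests wholly on assumption. Simulated patients divide their visits between one solo doctor (20–40% of visits) and a group of 2, 3 or 5 doctors in which the usual doctor takes 50–90% of the group's visits. The denominator is all such simulated patients.

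| Total visits | Group size | Assigned to the less-attended practice | False tie |
|---|---|---|---|
| 4 | 2, 3, 5 | 0% | 0–13.5% |
| 6 | 2, 3 | 0% | 1.2–18.9% |
| 6 | 5 | 0–3.2% | 1.2–18.8% |
| 10 | 2, 3, 5 | 0.1–18.8% | 0.9–15.5% |

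A second set of assumptions (Poisson mean of 6 visits, 60–70% in the group, usual doctor 50–85%), restricted to patients who used both practices with the group ahead, gives 1.0–19.4% and 9.2–32.2%. Neither range is a share of trial patients; it would have to be multiplied by the unknown proportion who attend in this way.

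**5. Effect on the estimate.** If a fraction f of all analysed patients were attributed to a practice with an unrelated arm, a 5-point effect becomes 5 × (1 − f): 4.95 at f = 1%, 4.75 at 5%, 4.5 at 10%. These values of f are illustrative. They also overstate the loss, since the patient does attend the chosen practice to some extent.

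**6. Ties in replicate 2.** For a patient aged 31 to 64, ODB claims hold no prescriptions. Neither the prescription count nor the draw among prescribers can then be carried out on the data named.

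**The case against.** The best defence is that the rule is offered as a stricter definition of the physician-patient relationship, and a main-doctor rule is exactly that. Other parts of the article also work by doctor: the message is directed at doctors, the Recruitment section calls the physician the unit of analysis and confirms patients by the study physician's plurality of prescriptions, and the Analyses section makes trial arm a physician-level variable. Doctors nest within practices, so each patient still ends up in one practice and one arm, chosen without regard to allocation. This much stands: the doctor-level rule is a defensible definition of the main doctor, and it introduces no bias in favour of any arm. It does not explain why attribution should leave the practice level, when the contamination argument treats the practice as exposed as a whole and the main rule follows it.

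Four stronger readings are tempting but not supported.
- *The error always runs towards smaller practices.* Between a solo doctor and a group, only the group can lose. In general, though, what matters is how dispersed the visits are within a practice; in the third example the larger practice gains the patient.
- *The solo-versus-group subgroup is distorted.* The Subgroup analyses section does not say that it uses this attribution; the main rule is by practice.
- *The rule brings back the mixing it was meant to remove.* Multiple counting is fully removed. A practice-level rule would also leave some visits elsewhere: 40% in the first example.
- *False ties are misassignments.* They go first to the doctor with the most prescriptions, who may well be in the leading practice.

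**Conclusion.** The mismatch of levels is real and follows from the text alone: practices are randomised and hold the patients in the main analysis, while the sensitivity rule and its tie-breaks count by doctor. A patient it misplaces is in another arm with probability 75% (replicate 1) or 81.25% (replicates 2 and 3). How many patients are misplaced cannot be derived; the simulated ranges start at zero and rest on assumed visit patterns among patients of unknown number. The expected consequence is slight dilution towards no difference, plus avoidable ties that cannot be settled by prescriptions for replicate 2 patients under 65. It is confined to a sensitivity analysis and leaves the primary analysis, sample size and stated power as they are. It is worth correcting because the correction is nearly free.

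**What to change.** Reword the rule so that primary care visits are summed over all physicians in a practice, the randomised unit, and the patient is assigned to the practice with the plurality. Apply the tie-breaks between practices only, with prescriptions likewise summed by practice. Choose a physician within that practice only where a physician-level variable is needed.

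Summing removes the false ties but not genuine ones. For replicate 2 patients under 65, the last step should be a random draw among the tied practices that does not require prescription data.

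Cost: a sentence or two in the plan, and grouping by practice instead of physician; practice address is already linked to each doctor. The drawback is a small departure from a main-doctor definition of the relationship, so the doctor-level version can be kept as a secondary check.

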### Proposed sample size

We wished to have adequate power to detect modest changes in the way physicians practice. Based on the median absolute effectiveness of PEMs estimated from the Grimshaw review (8%) [7], it would be important to detect 5% and 10% absolute improvements in our target behaviours. Even 5% improvements in the prevalence of evidence-based care for these common conditions will be an important achievement, with significant health benefits for many Ontarians.

In pilot data, the baseline-prescribing rate of ACE inhibitors in persons with diabetes was 36%, and the intra-class correlation for ACE inhibitor use by patients clustered within physicians was 9.2%. With an assumption that one-half of doctors work in solo practices, we ran these data testing power at a mean of three patients and ten patients per practice. Monte Carlo simulations demonstrated that a trial with 1250 practices per arm, with 10 patients per practice and an alpha of 0.05 will provide more than 98% power to detect a 10% absolute increase in the rate of ACE inhibitor use, more than 97% power to detect a 5% absolute increase, and more than 98% power to distinguish between the effects of the combined intervention and either alone, assuming the combined effect to be additive.

Because the baseline rates of the other interventions are comparable or lower (screening for retinopathy, diuretic use, aggressive blood pressure-reducing, and cholesterol-lowering therapies), and the number of patients per practitioner with these conditions is the same or higher, we will have adequate power to detect similar absolute increases for those endpoints.

Later, with the addition (see Table 1) of two groups in the second (patient reminder note) and third (theory-based outsert) replicates, a less comprehensive, but approximate simulation suggested that the impact on power would be minor and would most certainly be greater than the often used target of 80%. The research opportunity that this modification presented was judged to outweigh the likely loss of power. Therefore, we maintained 1,250 practices in the two groups that did not receive an outsert with ***informed***, and assigned 625 practices to each of the four groups who were sent an outsert.

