### Analyses

We hypothesize that the active intervention arms will be superior to control, similarly effective to each other, and with some additive effect when both are delivered. Analyses will be concentrated on this hypothesis.

The study employs a cluster randomized design. The analysis will be carried out using multi-level, hierarchical, logistic regression models, with the trial arm being a physician-level variable, and the prescribing (or screening) outcome a patient-level variable. These models account for clustering of patients within practices, and the consequent lack of independence of prescribing outcomes within a given physician's place of practice [55]. No place-of-practice characteristics, aside from the arm of the trial and baseline adherence to guidelines, will be entered into the model in the primary analysis. With so many physicians randomized to each arm, we anticipate that measured and unmeasured physician factors that might affect the outcome will be equally distributed between the arms. Moreover, including more place-of-practice characteristics in the model would reduce the statistical power to detect the primary outcome.

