If passive dissemination of PEMs is shown to be effective, this study may give professional, administrative, and patient organizations interested in change toward evidence-based practice the impetus to develop systematic programs for practice change using PEMs. If shown to be ineffective, use of PEMs as a single practice change intervention would be discouraged, thereby eliminating waste and turning research attention toward other interventions, including a possible role for PEMs as one element in a multi-faceted intervention. If effectiveness is shown to vary by disease problem, barrier, subgroup of practitioner, or any other factor, this study will help inform how different kinds of PEMs should be used in different situations and health problems.

While no economic analysis has been proposed, pending a determination of the effectiveness of PEMs in changing practice, we will collect all costs attributable solely to PEM development, design and dissemination. If the intervention is effective, we will work to set up an initial cost analysis, in which the health care utilization and prescribing changes, if any, of the intervention will be assessed in view of the marginal costs of the PEM intervention. We also will approach professional bodies and patient advocacy groups to offer help in developing PEM strategies for health care quality improvement.

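### Replicate 1 has three primary outcomes, no rule for combining them, and a single unsplit alpha of 0.05

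*Protocol article*

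**What the plan says.** - **Primary outcome.** Table 2 (under Allocating participants to trial groups) gives replicate 1 the percentage "of target patients receiving an ACE inhibitor, % receiving 2 or more antihypertensive, and % receiving lipid-lowering drug". Replicates 2 and 3 have one outcome each: the percentage "of target patients receiving complete eye exam from optometrist or ophthalmologist" and the percentage "of target patients receiving a diuretic".
- **Hypothesis.** The Analyses section states: "We hypothesize that the active intervention arms will be superior to control, similarly effective to each other, and with some additive effect when both are" given. The model enters trial arm as a physician-level variable, and no contrast is singled out as the one that decides.
- **Error rate.** Alpha appears once, under Proposed sample size: "a trial with 1250 practices per arm, with 10 patients per practice and an alpha of 0.05". The article gives no sidedness and no split. The simulation behind it used the baseline rate and intra-class correlation of ACE-inhibitor use. Adequate power for the other endpoints is then asserted by analogy.
- **Use of the result.** The Discussion says what follows if PEMs work ("If passive dissemination of PEMs is shown to be effective, this study may give professional, administrative, and patient organizations") and what follows if they do not.

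**The concern.** The protocol treats three endpoints as one primary outcome. Different combining rules can give opposite conclusions from the same data. A gain in lipid-lowering prescriptions alone is a positive primary result under an any-one rule, a negative one under an all-three rule, and a secondary observation if ACE-inhibitor use leads. If the three are simply tested at 0.05 each, the stated 5% does not describe the error rate of the replicate's conclusion. The choice of rule would also remain open after the results are known. The power statement is affected too, because it was simulated for one of the three outcomes at unadjusted alpha.

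**Working it through.** **Inputs from the protocol (Proposed sample size).** Baseline 36%; intra-class correlation 0.092; 1,250 practices per arm; 10 or 3 patients per practice; increases of 5 or 10 points; alpha 0.05.

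**Assumptions that are not in the protocol.** Two-sided tests; any one success counts; a common correlation ρ between the three outcomes, varied from 0 to 0.8.

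**Step 1: reproduce the stated power.** With m patients per practice:

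- design effect = 1 + (m − 1) × 0.092
- effective n per arm = 1250m / design effect
- SE = √{[p₁(1 − p₁) + p₂(1 − p₂)] / effective n}
- power ≈ Φ(difference / SE − z)

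For 36% vs 41% the numerator is 0.2304 + 0.2419 = 0.4723.

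- m = 10: design effect 1.828, effective n 6,838, SE 0.00831, ratio 0.05/0.00831 = 6.02. Power = Φ(6.02 − 1.96), over 99.9%.
- m = 3: design effect 1.184, effective n 3,167, SE 0.01221, ratio 4.09. Power = Φ(4.09 − 1.96) = 98.4%.

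Combined versus single (41% vs 46%) gives over 99.9% and 98.0%. The protocol gives lower bounds of 97% for 5 points and 98% for the combined comparison, both for 10 patients per practice, and these are met.

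**Step 2: false-positive rate for replicate 1.** For three independent outcomes on one contrast:

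- either direction: 1 − 0.95³ = 14.3%
- benefit direction only: 1 − 0.975³ = 7.3%

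Correlation lowers these. A simulation of normal test statistics (one million draws, four equal arms, shared control) gives:

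| Tests, any one success counts | Direction | ρ = 0 | ρ = 0.5 | ρ = 0.8 | One test |
|---|---|---|---|---|---|
| Pooled PEM vs none, 3 outcomes | either | 14.3% | 12.5% | 9.8% | 5% |
| Pooled PEM vs none, 3 outcomes | benefit | 7.4% | 6.3% | 4.9% | 2.5% |
| 3 active arms vs control, 3 outcomes | either | 33.1% | 29.4% | 23.5% | 5% |
| 3 active arms vs control, 3 outcomes | benefit | 17.7% | 14.9% | 11.8% | 2.5% |

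If 0.05 was meant as one-sided, the pooled contrast gives 9.3% (ρ = 0.8) to 14.3% (ρ = 0) against 5%. If all three outcomes had to succeed on the pooled contrast, the rate would be under 1%.

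**Step 3: power after a split over three outcomes.** At 0.05/3 = 0.0167 two-sided, z = 2.39.

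- 36% vs 41%, m = 10: Φ(6.02 − 2.39), over 99.9%.
- 36% vs 41%, m = 3: Φ(4.09 − 2.39) = 95.5%.
- 41% vs 46%, m = 3: 94.8%.

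**The case against.** **Alpha allocation belongs in an analysis plan.** That plan is not shown, and the absence of a testing order from an article is no fault. This stands for the detail of the testing procedure. It does not cover what the article itself sets down, which is three endpoints entered as primary beside one undivided alpha. Which result answers the replicate's question is for the protocol to fix.

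**The any-one rule is not in the document.** This is correct. The hypothesis can be read as a joint claim, and under an all-three rule there is no inflation. The article states neither rule, so the inflation figures are conditional.

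**The design is factorial.** Table 1 crosses insert with outsert, and it is disputed whether separate factors need joint error control. This weakens any count built on every active arm versus control. It leaves the three-outcome problem, which is present with only one contrast.

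**Two stronger readings are not supported.**

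- A reader might infer that the chance of a false finding that PEMs work is about 29% instead of 5%. That figure needs nine tests, any success counting, a correlation of 0.5 and results in either direction. A false finding of benefit under the same assumptions is about 15%, and its comparator is 2.5%.
- A reader might extend the point to replicates 2 and 3 because they have five active groups. Each has a single primary outcome. The extra groups are described as a later addition, and the theory-based versus standard outsert comparison sits under Ancillary studies. Treating all five arms as one primary family is not what the text says.

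**Conclusion.** The point holds for replicate 1. Three outcomes are listed as primary with no any/all rule and no lead outcome, the only alpha is a flat 0.05, and power was simulated for ACE-inhibitor use alone. If each outcome is tested at two-sided 0.05 and any success counts, the false-positive rate on one pooled contrast is two to nearly three times nominal in either direction, and about the same multiple for a false benefit. Adding separate comparisons of each active arm with control raises it further, to the second pair of rows in the table. The size rests on the assumed rule, sidedness, contrast and outcome correlation, none of which the article gives, so it should be quoted as a range with those assumptions attached. That the rule is open does not depend on them.

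**What to change.** In Table 2 and the Analyses section, before outcome data are seen, do one of the following for replicate 1:

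1. Name ACE-inhibitor use, the endpoint the trial was sized on, as the single primary outcome, with the other two as secondary.
2. Keep all three and control the family-wise error at two-sided 0.05, by Bonferroni at 0.0167 per outcome or by Holm.

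In either case, name one deciding contrast and make the others secondary. If option 2 is to carry further contrasts as confirmatory, test them in sequence within each outcome, at that outcome's 0.0167 throughout. The level of the later steps must be written down. Suppose one format works and the other is null on all three independent outcomes. Later steps run at Holm's levels then give 1 − 0.9833 × 0.975 × 0.95 = 8.9%, and at 0.05 each 1 − 0.95³ = 14.3%. Holding 0.0167 throughout gives 1 − 0.9833³ = 4.9%.

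State the sidedness of alpha, and restate power at the level adopted (step 3 gives the values for 0.0167). Under option 2 the cost is a slightly lower stated power, under 3 points for a 5-point increase with 3 patients per practice (98.4% to 95.5%) and negligible with 10. No extra practices or data are needed.
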